## **5.3 Subject Exclusion Criteria**

- Previous vaccination with an investigational vaccine or a rabies vaccine

- Use of a investigational or non-registered drug or vaccine other than the study vaccine(s) within 30 days preceding the first study immunization, or planned use up to 30 days after the third immunization
- Chronic administration (defined as more than 14 days) of immunosuppressants or other immune-modifying drugs within six months prior to the first immunization. This includes any dose level of oral steroids or inhaled steroids, but not topical steroids
- Confirmed or suspected immunosuppressive or immunodeficient condition, including human immunodeficiency virus (HIV) infection
- Confirmed or suspected autoimmune disease
- History of allergic reactions or anaphylaxis to immunizations or to any vaccine component
- History of serious allergic reactions to any substance, requiring hospitalization or emergent medical care
- History of allergy to tetracycline, doxycycline, nickel or Imidazole
- History of splenectomy
- Laboratory evidence of liver disease (alanine aminotransferase [ALT] greater than the upper limit of normal of the testing laboratory = 49.6 U/L).
- Laboratory evidence of renal disease (serum creatinine greater than the upper limit of normal of the testing laboratory = 0.5 mg/dL (44.2  $\mu$ mol/L), or more than trace protein or blood on urine dipstick testing).
- Laboratory evidence of hematologic disease (absolute leukocyte count  $<5,300/\text{mm}^3$  or  $>15,300/\text{mm}^3$ , absolute lymphocyte count  $<2,300/\text{mm}^3$ , platelet count  $<133,000/\text{mm}^3$ , or hemoglobin  $<9.0$  g/dL).
- Chronic skin condition that could interfere with vaccine site reactogenicity assessment
- Administration of immunoglobulins and/or any blood products within the three months preceding the first study immunization or planned administration during the study period.
- Simultaneous participation in any other interventional clinical trial
- Acute or chronic pulmonary, cardiovascular, hepatic, renal or neurological condition, severe malnutrition, or any other clinical findings that in the opinion of the PI may increase the risk of participating in the study
- Other condition that in the opinion of the PI would jeopardize the safety or rights of a participant in the trial or would render the participant unable to comply with the protocol

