## **8 STUDY PROCEDURES/EVALUATIONS**

### **8.1 Standard operating procedures (SOPs)**

The Investigators will maintain detailed SOPs for vaccine transport, storage, formulation, reconstitution and administration. All staff and investigators will be trained in the SOPs relevant to their duties and will sign copies of the SOPs to document this training. Copies of SOPs will be available for inspection and review by the DMID, USAMMDA, GSKBio, WRAIR and study monitors. During the study SOPs may be modified to improve them and new SOPs may be developed as needed to improve operations and ensure adherence with the protocol.

The following SOPs will be followed (additional SOPs may be developed and added):

- Recruitment
- Community informed consent
- Individual informed consent
- Field team organization
- Physical examination
- Management of anaphylaxis
- Case management of uncomplicated and severe malaria
- Management of abnormal laboratory tests
- Completion of CRFs
- Transport of vaccines and adjuvants
- Vaccine preparation and administration
- Vaccine accountability, handling, storage, disposition and destruction
- Randomization
- Unblinding
- Quality control and quality assurance
- Study documentation
- Adverse event reporting
- Protocol deviations
- SAE reporting
- Provisions for study suspension
- Malaria thick smear preparation and reading
- Specimen collection and handling
  - Blood collection
  - Urine collection
  - Specimen transport
  - Specimen reception
  - Serum separation
  - Specimen storage

- Specimen shipping overseas
- Waste management
  - Sharps handling and disposal
  - Biologic waste handling and disposal
  - General waste handling and disposal
- Safety
  - Spill management
  - Exposure to body fluids
- Equipment maintenance and quality control SOPs (Reflotron PLUS, AcT-Diff, Centrifuge)

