|                           | Normal Range                                   | Grade 1                                                          | Grade 2                                                         | Grade 3                                                           | Grade 4 (SAE)                                  |
| Creatinine                | 0.2–0.5 mg/dL (15.2–44.2 µmol/L) c  | 44.2 – 91.5 µmol/L (0.5-1.0 mg/dL)                               | 91.6 – 183 µmol/L (1.1-2.0 mg/dL)                               | 183.1 – 366 µmol/L (2.1-4.0 mg/dL)                                | > 366 µmol/L (>4.1 mg/dL) or dialysis required |
| ALT                       | 3.9 – 49.6 U/L a                    | 49.7-124 U/L                                                     | 124.1 – 248 U/L                                                 | 248.1 – 496 U/L                                                   | > 496 U/L                                      |

aDetermined and adapted from normal children in Donéguébougou, a rural Malian village and malaria vaccine trial site

b From Lugada, E. S. et al. Population-Based Hematologic and Immunologic Reference Values for a Healthy Ugandan Population. *Clin Diag Lab Immunol*, 11, 29-34.

c From Current Pediatric Diagnosis & Treatment, 17th edition, 2005.

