## **10.11 Data Safety and Monitoring Board (DSMB)**

An independent DSMB will be constituted by DMID to review safety data at specified intervals prior to each dose escalation. The role of the DSMB is to provide safety oversight over the conduct of the trial. It will review blinded safety data before each dose escalation and advise on progression to the next dose level. The DSMB will hold two conference calls to review the safety data generated from the trial up to that point. These calls will occur as soon as possible after the completion of the 7-day

surveillance period following each of the first 2 immunizations of cohorts 1 and 2. The first call will thus occur approximately one week before the first immunization with the 25 µg dose level of FMP2.1, and the second will occur approximately one week before the first immunization with the 50 µg dose level (Figure). The purpose of these conference calls will be to review the accumulated safety data to advise whether or not the study can proceed with the dose escalation, and whether the trial can proceed generally. In the event that the DSMB identifies a safety concern, the collaborative group including the investigators, DMID, WRAIR, GSK and USAID will review all safety data to decide whether to give the next sequential dose. Senior investigators and representatives from USAMMDA, DMID, WRAIR, GSK and USAID will be invited to but not obligated to participate in the conference calls during open sessions, which will be followed by closed sessions including only DSMB members.

[figure not shown]

**Figure.** Timeline for safety reviews by DSMB. Arrows down indicate immunization safety data included in safety review. Arrows up indicate review results in recommendation to proceed with immunization.

The DSMB will meet after the 7-day surveillance period following the last immunization of cohort 3 to review safety data and provide advice to the sponsors and investigators with regard to dose selection for the subsequent Phase 2 trial.

The investigator will inform the DSMB of:

- All subsequent protocol amendments, informed consent form changes or revisions of other documents originally submitted for review
- Serious adverse events (SAEs), grade 3 adverse experiences and grade 2 abnormalities of laboratory tests occurring during the study, regardless of relationship to the study vaccine
- New information that may affect adversely the safety of the subjects or the conduct of the study.

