### **Clinical laboratory parameters**

Hematological (CBC) and biochemical (ALT, creatinine) laboratory parameters will be measured at specific time points, Days 0, 7, 30, 37, 60, 67 and 90. Clinically relevant abnormal values based on reference intervals determined in rural Malian children will be tabulated and a trend analysis could be performed if deemed necessary. Laboratory abnormalities will be graded on a scale of 1-4 as defined in relevant SOPs.

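### The laboratory toxicity table overlaps its own normal ranges at three eligible boundaries, and its two creatinine scales disagree next to the Grade 4 limit

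*Protocol*

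**What the plan says.** Protocol section 10.3 contains a table of laboratory toxicity grades, numbered 12, with a normal range and Grades 1 to 4 for each parameter. Grade 4 is labelled as an SAE.

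- **Creatinine.** Normal is "0.2–0.5 mg/dL (15.2–44.2 µmol/L"); Grade 1 is "44.2 – 91.5 µmol/L (0.5-1.0 mg/dL"); Grade 3 is "183.1 – 366 µmol/L (2.1-4.0 mg/dL"). Grade 4 is above 366 µmol/L, with above 4.1 mg/dL in brackets, or need for dialysis.
- **Lymphocytes.** Normal is 2,300-9,500/mm3; Grade 1 is 1,000-2,399/mm3.
- **WBC.** Normal is 5,300-15,300/mm3; the high Grade 1 band is 15,299-16,500/mm3.
- **Platelets.** Normal is 133,000-523,000/mm3; the only high-side grade is Grade 3, above 1,000,000/mm3.

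Section 5.3 excludes a child for "serum creatinine greater than the upper limit of normal of the testing laboratory = 0.5 mg/dL", for lymphocytes below 2,300/mm3 or for WBC above 15,300/mm3. Values exactly at those limits are therefore eligible.

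Section 12.5.3 (Clinical laboratory parameters) does not cite the table. It says "Laboratory abnormalities will be graded on a scale of 1-4 as defined in relevant SOPs", and it bases abnormal values on reference intervals from rural Malian children. The table's footnotes give a Ugandan source for lymphocytes and a paediatric textbook for creatinine. Under section 10.11 the investigator reports to the DSMB "grade 3 adverse experiences and grade 2 abnormalities of laboratory tests occurring during the study".

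**The concern.** A grading table should put each value in one category. Here some values that the protocol calls normal, and accepts at entry, are also a Grade 1 abnormality. A child could then count as having a laboratory abnormality at the Day 0 draw, before any vaccine, or not, depending on which column the grader reads first.

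Safety is the primary objective, section 10.2.1 counts laboratory-detected changes as adverse events, and section 12.5 requires laboratory abnormalities in the primary report. The number of Grade 1 findings per dose group should not depend on the reader.

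The unit disagreement matters for a different reason. It sits beside the limit at which a creatinine result is labelled an SAE, and SAE counts feed the pause rule in section 10.9.

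**Working it through.** **Inputs.** Normal ranges and grades come from the table in section 10.3, and eligibility limits from section 5.3. The unit factor is the protocol's own: 44.2 µmol/L ÷ 0.5 mg/dL = 88.4 µmol/L per mg/dL. Both sections print that pair.

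**Step 1: values in two categories.** Each printed range is read as including its end points.

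| Parameter | Normal | Grade 1 | Excluded at entry | Normal, eligible and Grade 1 |
|---|---|---|---|---|
| Creatinine | up to 0.5 mg/dL (44.2 µmol/L) | from 0.5 mg/dL (44.2 µmol/L) | above 0.5 mg/dL | 0.5 mg/dL (44.2 µmol/L) |
| Lymphocytes, /mm3 | from 2,300 | up to 2,399 | below 2,300 | 2,300-2,399 |
| WBC, /mm3 (high side) | up to 15,300 | from 15,299 | above 15,300 | 15,299-15,300 |

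The lymphocyte overlap covers 2,399 − 2,300 + 1 = 100 integer values and is the widest. The WBC overlap covers two. The creatinine overlap is one boundary value; if results are reported to one decimal in mg/dL (assumption), it is one of four normal values (0.2, 0.3, 0.4, 0.5).

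Other boundaries join cleanly: ALT 49.6/49.7 U/L, hemoglobin 8.4/8.3 g/dL, platelets 133,000/132,999, and WBC on the low side 5,300/5,299. Shared end points are therefore not the table's convention.

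**Step 2: the two creatinine scales.** Converted value = mg/dL × 88.4.

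| mg/dL limit | Converted, µmol/L | Printed, µmol/L |
|---|---|---|
| 0.2 | 17.7 | 15.2 |
| 0.5 | 44.2 | 44.2 |
| 1.0 | 88.4 | 91.5 |
| 2.0 | 176.8 | 183 |
| 4.0 | 353.6 | 366 |

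The 0.5 limit reproduces. The upper grade limits do not: 91.5 ÷ 1.0, 183 ÷ 2.0 and 366 ÷ 4.0 all give 91.5 per mg/dL, so the grade bands follow a different factor from the normal limit.

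For 4.1 mg/dL, 4.1 × 88.4 = 362.4 µmol/L. In µmol/L that lies within 183.1-366 and is Grade 3. In mg/dL it is above the Grade 3 end (4.0) but not above 4.1, so it has no grade. Conversely, 366 ÷ 88.4 = 4.14 mg/dL. On a one-decimal grid from 0.2 to 4.5 mg/dL, 4.1 is the only value that the two scales class differently.

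**Step 3: values with no grade.** Platelets of 523,001-1,000,000/mm3 are above normal and ungraded, after which the table goes straight to Grade 3. Lymphocytes above 9,500/mm3 and hemoglobin above 12.4 g/dL are also ungraded.

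**Step 4: possible size.** The protocol gives no distribution of results. As an assumption, let a share p of children have a value on an overlap at a given draw. The expected number in a dose group of 30 is 30p, and the chance of at least one is 1 − (1 − p)^30.

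| p (assumed) | Expected of 30 | Chance of at least one |
|---|---|---|
| 5% | 1.5 | 0.79 |
| 10% | 3.0 | 0.96 |
| 25% | 7.5 | above 0.99 |

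**The case against.** **The intended limits can be guessed.** Section 5.3 repeats the normal limits for all three parameters, and some low-side bands are built as the limit minus one. The overlaps therefore look like slips. That is plausible, but a grader following the table still has two answers for the same value.

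**The consequences are small.** This stands in large part. The overlaps lie between normal and Grade 1. A reader might infer that they distort the DSMB escalation reviews, but laboratory reporting there is set at Grade 2, and no overlap moves a value into or out of Grade 2. A reader might also infer that real vaccine effects are diluted. The documents do not show this: longer-term safety in section 12.5.3 compares hemoglobin, creatinine and ALT levels, the trial is not powered for group comparisons, and a Day 0 panel identifies baseline values. A creatinine of 4.1 mg/dL is about eight times the upper limit (4.1 ÷ 0.5 = 8.2), so it should be rare in children screened as healthy, and section 10.7.1 defines SAEs independently.

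**The SOPs may repeat the table.** This also stands. Section 8.1 says "During the study SOPs may be modified to improve them and new SOPs may be developed as needed", so a reader might infer that the analysis uses a different or shifting scale. The SOPs are not shown, and that same sentence ties changes to adherence to the protocol. What is shown is a missing cross-reference.

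**High platelets may be ungraded on purpose.** The table also leaves high hemoglobin and high lymphocytes ungraded, so the platelet band is not by itself an error. It needs a statement of intent.

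**Conclusion.** The table contradicts its own normal ranges at three boundaries, all at values that section 5.3 accepts: lymphocytes 2,300-2,399/mm3, creatinine 0.5 mg/dL (44.2 µmol/L) and WBC 15,299-15,300/mm3. Grade 1 counts depend on which column is applied. Its creatinine limits also disagree between units, leaving 4.1 mg/dL as Grade 3 on one scale and ungraded on the other, beside the limit labelled SAE.

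Severity is minor. These are operative safety limits that would misclassify values if followed as printed, but no DSMB reporting threshold, primary endpoint or powered comparison is shown to change. How many results are affected is unknown; the counts above rest on assumed shares. The conclusion rests on reading printed ranges as including their end points and on the protocol's own factor of 88.4. The documents do not support the broader claim that laboratory toxicity has no single definition.

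**What to change.** - Reconcile the table in section 10.3 with its own normal ranges and with section 5.3, so that no value falls in two categories.
- Make the mg/dL and µmol/L creatinine limits agree at every grade, including the step from Grade 3 to Grade 4.
- State whether platelets of 523,001-1,000,000/mm3 are deliberately ungraded.
- In section 12.5.3, cite this table as the grading scale in place of the SOPs. Renumber it first, because the event-detection table in section 12.4 is also Table 12.
- Align the section 12.5.3 wording on rural Malian reference intervals with the table's footnotes.

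Which clinical cut-offs are right is for the sponsor to decide. The cost is an amendment to one table and its cross-references, plus changes to any grade limits already programmed. No test, visit or sample size changes.

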## 10.4 Assessment of causality

Every effort will be made by the investigator to explain each adverse event and assess its causal relationship, if any, to administration of the study vaccine(s).

The degree of certainty with which an adverse event can be attributed to administration of the study vaccine(s) (or alternative causes, e.g., natural history of the underlying diseases, concomitant therapy, etc.) will be determined by how well the event can be understood in terms of one or more of the following:

- Reaction of similar nature having previously been observed with this type of vaccine and/or formulation.
- The event having often been reported in literature for similar types of vaccines.
- The event being temporally associated with vaccination or reproduced on re-vaccination.

All solicited local (injection site) reactions will be considered causally related to vaccination. The investigators will assess the causality of all other adverse events using the following method:

In your opinion, did the vaccine(s) possibly contribute to the adverse event?

- NO : The adverse event is not causally related to administration of the study vaccine(s). There are other, more likely causes and administration of the study vaccine(s) is not suspected to have contributed to the adverse event.
- YES : There is a reasonable possibility that the vaccine contributed to the adverse event.

If an AE is determined not to be causally related to administration of a study vaccine, the investigators will specify the likely cause if one can be determined.

## **10.5 Following-up of adverse events and assessment of outcome**

Investigators will follow up subjects with serious adverse events until the event has resolved or until the condition has stabilized regardless of when this outcome occurred in relation to the study conclusion. Investigators will follow up participants with non-serious adverse events until the participant completes the study. Clinically significant laboratory abnormalities, as well as any adverse event, will be followed up until they have returned to normal, or until a satisfactory explanation has been provided. Reports relative to the subsequent course of an adverse event noted for any subject will be submitted to the Study Monitor.

Outcome will be assessed as Resolved, Resolved with Sequelae, Ongoing, or Death.

## **10.6 Clinical malaria**

Clinical malaria will be recorded in the same fashion as other adverse events. In general, uncomplicated malaria will constitute an AE and severe malaria will constitute an SAE. Formal clinical case definitions of these conditions will not be used and study clinicians may exercise their judgment to hospitalize cases that do not meet standard definitions of severe malaria.

## **10.7 Serious adverse events**

In 2004 the under-5 year age group mortality rate in Mali was 21.9%. While the children participating in this study will receive better medical care than most Malian children do, some hospitalizations and even deaths are likely in the normal course of events in this population.

### **10.7.1 Definition of a serious adverse event**

A serious adverse event is any untoward medical occurrence that results in death, is life threatening, results in persistent or significant disability/incapacity, requires in-patient hospitalization or prolongation of existing hospitalization or is a congenital anomaly/birth defect in the offspring of a study subject. In addition, important medical events that may jeopardize the participant or may require intervention to prevent one of the other outcomes listed above will be considered serious.

- Life threatening—definition: An adverse event is life threatening if the participant was at risk of death at the time of the event; it does not refer to an event, which hypothetically might have caused death, if it were more severe.
- Disabling/incapacitating—definition: An adverse event is incapacitating or disabling if the event results in a substantial disruption of the participant's ability to carry out normal life functions. This definition is not intended to include experiences of relatively minor medical significance such as headache, nausea, vomiting, diarrhea, influenza, and accidental trauma (e.g. sprained ankle).
- Hospitalization: In general, hospitalization signifies that the participant has been detained (usually involving at least an overnight stay) at the hospital or emergency ward for treatment that would not have been appropriate in the physician's office or outpatient setting.

### **10.7.2 Reporting serious adverse events**

All serious adverse events will be:

- Recorded on the appropriate serious adverse event case report form
- Followed through resolution by a study physician
- Reviewed by a study physician

Any AE considered serious by the Principal Investigator or Subinvestigator or meets the aforementioned criteria must be submitted on an SAE form to PPD Development, NIAID's pharmacovigilance contractor, which will notify USAMMDA as the Sponsor as well as DMID, USAID, GSKBio, and the University of Maryland International Regulatory Affairs Coordinator of any SAEs, with in the timelines required by each of these parties.

#### **10.7.2.4 HSRRB SAE REPORTING CONTACT INFORMATION**

Unanticipated problems involving risk to volunteers or others, serious adverse events related to participation in the study, and all volunteer deaths should be promptly reported by [contact]), by e-mail ([[contact]](mailto:[contact])), or by [contact]) to the U.S. Army Medical Research and Materiel Command's Human Subjects Research Review Board. A complete written report should follow the initial notification. In addition to the methods above, the complete report can be sent to the U.S. Army Medical Research and Materiel Command, ATTN: MCMR-ZB-P, [name].

#### **10.7.2.5 REGULATORY REPORTING**

Following notification via PPD from the investigator, USAMMDA, the IND sponsor, will report events that are both serious and unexpected and that are associated study product(s) to the FDA within the required timelines as specified in 21 CFR 312.32: fatal and life threatening events within 7 calendar days (by phone or fax) and all other serious adverse events in writing within 15 calendar days. All serious events designed as "not associated" to study product(s), will be reported to the FDA at least annually in a summary format.

#### **10.7.2.6 SAE reporting procedures**

The study clinician will complete a Serious Adverse Event Form within the following timelines:

- All deaths, whether related or unrelated, will be recorded on the Serious Event Form and sent by fax or electronic mail immediately upon discovery of the death regardless of availability of complete information. For initial reports provided via telephone, a written report via electronic mail or fax will be provided within 24 hours of discovery of death by investigators. Follow-up reports will be provided as complete or additional relevant information is available.
- Serious adverse events other than death, regardless of relationship, will be reported via fax by the site immediately upon discovery of the experience regardless of availability of complete information. For initial reports provided via telephone, provide a written report via electronic mail or facsimile within 72 hours of becoming aware of the event. Follow-up reports will be provided as complete or additional relevant information is available.

Other supporting documentation of the event may be requested by the pharmacovigilance contractor and should be provided as soon as possible.

All SAEs will be followed until satisfactory resolution or until the Principal Investigator or Subinvestigator deems the event to be chronic or the patient to be stable.

Every serious adverse event that is not resolved at the time the initial written report is filed will have a follow-up report submitted when information is available. Any submitted report will be identified as "initial", "follow-up", or "medical monitor".

The initial notification will include:

- The study protocol number and the name of the PI
- The participant ID number, gender and age
- The date of onset of the SAE, and date of administration of study vaccine(s)
- Description of event

The PI will not wait to collect additional information to fully document the event before making notification of a serious adverse event. The telephone/e-mail report will be followed by a full written report using the SAE form within the CRF, detailing relevant aspects of the adverse events in question.

Formal surveillance will continue until stability or resolution of the event. However, in the event that instances of death or cancer in a study participant are brought to the attention of the investigator AT ANY TIME after cessation of the study AND suspected by the Investigators to be related to study medication will be reported to USAMMDA, DMID and GSKBio within four weeks of coming to the knowledge of the PI.

